### Methods/design

We will set up a single centre prospective sequential trial with two cohorts in a palliative HNSCC patient population. This study design is chosen in favour of a randomized controlled trial, because potential bias can be avoided as doctors develop a learning curve while working with the palliative model and could change their way of counselling. We aim to investigate the difference in effect of (prognostic) counselling without and with the use of OncologIQ Palliative by obtaining outcomes on decisional conflict, the amount of palliative treatment, palliative sedation or euthanasia, overall survival and QoL. The two cohorts in this study will be divided based on the type of prognostic counselling received. Cohort 1 will consist of patients who receive prognostic counselling without the model, reflecting the current clinical practice. Cohort 2 will comprise patients who receive additional prognostic counselling with the model. Additionally, we will conduct a qualitative evaluation through interviews among patients in cohort 2. This evaluation aims to investigate satisfaction with proactive care planning, including end-of-life discussions on preferred place of death and wishes for palliative sedation and euthanasia, following counselling with the use of OncologIQ Palliative.

Our hypothesis is that sharing personalized prognostic information on life expectancy with HNSCC patients in the palliative phase will empower patients throughout the decision-making process from the start of the palliative trajectory till death. More specifically providing this individualized prognostic information with the help of our prognostic model will lead to less decisional conflict and more satisfaction with the decision-making process. Additionally, we anticipate greater satisfaction with proactive care planning, including end-of-life discussions on preferred place of death and wishes for palliative sedation and euthanasia. Furthermore, when patients are optimally informed, they may choose palliative treatments less often, and it could lead to a higher QoL.

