#### Participants and eligibility criteria

To be eligible for participation in the clinical study and qualitative evaluation, individuals must meet specific criteria. These include patients with HNSCC in the palliative phase and tumours situated in the oral cavity, oropharynx, nasopharynx, hypopharynx, supraglottic larynx, glottis larynx and unknown primary. Additionally, participants must have adequate understanding of the Dutch language and be aged 18 years or older. Exclusion criteria encompass individuals who are illiterate, have insufficient proficiency in the Dutch language, or lack decision-making capacity to consider their own treatment choices due to factors such as mental incapacitation.

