### Recruitment and study procedures

#### Clinical study

Patients who are transitioning into a palliative HNSCC trajectory will be consecutively approached to participate in the study. The investigator will start by screening eligible patients after their first or follow-up visit. Once the patient has been discussed in the RWHHT, the researcher will check whether the palliative trajectory is confirmed.

In cohort 1, during the visit in which the palliative trajectory is discussed, the physician will provide counselling without the individualized prognostic model. As part of standard care, the patient will then visit the nurse practitioner immediately after their appointment with the physician. During this visit, the nurse practitioner or the investigator will inform patients about the study and present the subject information sheet. Patients will be asked to participate, and the informed consent (IC) form will be collected digitally.

In cohort 2, during the visit in which the palliative trajectory is discussed, the physician will inform the patient about the option to receive additional individualized prognostic counselling on their life-expectancy using OncologIQ Palliative. Considering that most patients have prognostic inquiries when discussing the palliative trajectory (*‘Doctor*,* how long will I live?’)*, we would like to offer them the model’s prognostic information directly or in a follow-up consultation, according to their preference. We believe it is unethical to let them wait for several days if they want to receive more prognostic information right away. If patients opt not to receive their individually calculated prognosis, they will be counselled without the model and offered general information about prognosis. However, if patients prefer not to receive any information on prognosis, their preference will be respected. As part of standard care, the patient will directly visit the nurse practitioner after their appointment with the physician. During this visit, the nurse practitioner or the investigator will provide the patient with additional oral information and the subject information sheet. We will only inform patients if they have received counselling with the model. If these patients wish to continue participating, we will ask them to sign the IC digitally.

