### Outcome evaluation

#### Clinical study

The first outcome measure relates to the amount of decisional conflict and satisfaction with the decision-making process of patients after prognostic counselling. This will be assessed through a comparison of cohort 1 and cohort 2 on decisional conflict scores, measured using the DCS questionnaire (Appendix A) [38, 39]. This questionnaire measures: (a) personal perceptions of uncertainty in choosing options, (b) modifiable factors contributing to uncertainty, such as feeling uninformed, unclear about personal values, and unsupported in decision making, (c) effective decision making, such as feeling the choice is informed, values-based, likely to be implemented, and expressing satisfaction with the choice.

The secondary outcome measures relate to the effect of prognostic counselling on different factors, including: (1) overall survival, (2) palliative treatment, and (3) QoL.

*Overall survival* will be measured from the date of the start of the palliative trajectory until the date of death or the last follow-up visit. Survival outcomes will be compared between both cohorts.

*Palliative treatment* will be assessed by examining whether a patient underwent treatment and the type of treatment received. Data on treatment modalities will be collected for each patient by consulting the EPF.

*Quality of life (QoL)* of patients will be measured using the EORTC QLQ-C15-PAL questionnaire, a shortened version of the EORTC QLQ-C30 [40, 41]. This questionnaire is recommended for use in patients with advanced and incurable cancer with a short life expectancy. The EORTC QLQ-C15-PAL questionnaire consists of 15 questions across 10 domains: physical functioning, emotional functioning, fatigue, pain, dyspnoea, insomnia, appetite loss, constipation, nausea/vomiting, and global health status. In the domains of emotional functioning, physical functioning, and global health status, a higher score indicates a better QoL, while in the other domains, a lower score indicates a better QoL.

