### Challenges and resolutions

Launching this project with the vision to potentially implement OncologIQ Palliative as a future standard of care, we were met with a series of challenges. One such challenge, anticipated during the initial planning phase of the project, was the *short life expectancy and vulnerability* of the patient population. This vulnerability, stemming from their bad condition and issues with vital functions such as breathing and swallowing, as well as their short life span, can make it more difficult for patients to participate in research projects. However, we anticipated that most patients would respond positively to this project, as earlier research shows that patients consider life expectancy a very important topic in the palliative phase and, in the case of a poor prognosis, have a stronger preference for prognostic information presented in a specific quantitative manner. Taking into account this limited time and to minimalize the burden on patients, we are inviting them early in their trajectory to participate. Constantly keeping in mind that we cannot ask much from these patients, we aim to keep the burden for the patients as low as possible. For example, we are digitally sending out the questionnaires and conducting the interviews at their preferred location.

Furthermore, it remains crucial to understand *different individual patient preferences* for prognostic information. Earlier research among HNSCC patients indicated that in the hypothetical case of cancer recurrence and a poor prognosis they tend to express a stronger preference for quantitative individual prognostic information [21]. However, preferences vary widely among all individuals, and not all wish to receive quantitative data about their prognosis. Some may prefer a more qualitative approach, focusing solely on broader aspects of their condition. Another layer of complexity arises from the possible *distinct needs* between patients and their loved ones. While one of them might desire specific numerical probabilities on life expectancy, the other might prefer not to know. Balancing these perspectives could lead to difficulties during consultation sessions. Additionally, *communicating survival probabilities* effectively is essential. However, this can be confusing for patients and their caregivers, as presenting statistical information – such as the individualized chances of survival – requires specific skills.

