## Conclusion

Our results have the potential to lead to the availability of optimal outcome data on the individual life-expectancy of HNSCC patients in the palliative phase. This information can empower physicians in counselling patients by offering more accurate personalized prognostic insights, while also potentially improving patients’ and their loved ones’ understanding and preparedness regarding the situation. By providing a clearer prognosis, we anticipate a shift towards more patient-centred counselling. This could lead to greater patient empowerment, facilitating enhanced end-of-life discussions, and better proactive care planning as they are better prepared. As a result, patients may experience reduced decisional conflict and greater satisfaction with the decision-making process. In addition, we expect that when patients are optimally informed they will choose for less treatment in the palliative phase. All of these aspects can contribute to a better quality of life and quality of care for HNSCC patients in the last phase of their lives. If our findings are proven effective, we are devoted to implementing and offering counselling with OncologIQ Palliative structurally for all our palliative patients who wish to receive this information.

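### The treatment hypothesis is about patients choosing less palliative treatment, but treatment received in all patients cannot by itself show a change in choice

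*Protocol article*

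**What the plan says.** The hypothesis in Methods/design is worded as a patient decision: "when patients are optimally informed, they may choose palliative treatments less often". The Conclusion repeats it more firmly: "we expect that when patients are optimally informed they will choose for less treatment in the palliative phase".

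Under Outcome evaluation (Clinical study), palliative treatment "will be assessed by examining whether a patient underwent treatment and the type of treatment received". The source is the patient file and the population is everyone enrolled: "Data on treatment modalities will be collected for each patient by consulting the EPF".

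Elsewhere the article uses neutral wording. The abstract and Methods/design call the outcome the amount of palliative treatment, the abstract's discussion anticipates fewer treatments, and the secondary aims in the Background refer to differences in treatment between cohorts.

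The inclusion criteria concern disease phase, tumour site, language and age ("These include patients with HNSCC in the palliative phase and tumours situated in the oral cavity" and further sites). None requires that a palliative treatment was available or proposed.

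**The concern.** Undergoing treatment requires that an option exists and is offered, that the patient accepts it, and that the patient is still able to start. The hypothesis concerns acceptance, while the endpoint records the end of the whole sequence. A patient with no option, or one who deteriorates first, has the same value (no treatment) as an informed patient who declined.

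Such patients are plausible here. The article gives a median survival of five months, with individual survival from as little as one week, and refers to "This vulnerability, stemming from their bad condition and issues with vital functions such as breathing and swallowing".

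Two things could follow. A real change in choice would look smaller than it is. And if the share with no option or too ill to start differs between cohorts, receipt could fall, or a real fall could be hidden, for reasons unrelated to choice. At stake is whether a lower treatment rate in cohort 2 could be read as support for the hypothesis as worded.

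**Working it through.** **Plan's own figure.** There is none for this endpoint. The article's only sample-size calculation is for the decisional conflict score. From it I take only the planned cohort size, n = 80.

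**Inputs.** The article gives no offer or acceptance rates. All rates below are assumptions. Here *offered* means offered treatment and able to start it.

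**Formulas.**
- Proportion receiving treatment = share offered (q) × acceptance among those offered (a).
- Approximate power, two-sided 5%: Φ(|p₁ − p₂| / SE − 1.96), with SE = √{[p₁(1 − p₁) + p₂(1 − p₂)] / n}. Using a pooled variance under the null lowers each result by at most about 2 percentage points.

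**Step 1: dilution.** Suppose acceptance falls from 70% to 50% and the share offered is the same in both cohorts.

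| Share offered | Received, cohort 1 vs 2 | Power, all patients (n = 80) | Power, offered only (n per cohort) |
|---|---|---|---|
| 100% | 70% vs 50% | 75% | 75% (80) |
| 80% | 56% vs 40% | 54% | 66% (64) |
| 60% | 42% vs 30% | 36% | 53% (48) |

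Worked line for 60%:
- All patients: SE = √[(0.42 × 0.58 + 0.30 × 0.70)/80] = 0.0753. Then 0.12/0.0753 = 1.594, and Φ(1.594 − 1.96) = 0.36.
- Offered only: SE = √[(0.70 × 0.30 + 0.50 × 0.50)/48] = 0.0979. Then 0.20/0.0979 = 2.043, and Φ(2.043 − 1.96) = 0.53.

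Despite fewer patients, the analysis among those offered treatment has more power for a change in choice.

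**Step 2: a difference in receipt with no change in choice.** Suppose acceptance is 70% in both cohorts and only the share offered differs.

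| Offered, cohort 1 vs 2 | Received | Apparent change | Chance of p < 0.05 |
|---|---|---|---|
| 80% vs 80% | 56% vs 56% | 0 | 5% (nominal) |
| 80% vs 70% | 56% vs 49% | −7 points | about 14% |
| 80% vs 65% | 56% vs 45.5% | −10.5 points | about 27% |
| 80% vs 60% | 56% vs 42% | −14 points | about 43% |

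Reversing the shares (60% vs 80%) gives an apparent rise of 14 points, so the distortion can also hide a true reduction.

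**Step 3: could the share differ in this design?** The article describes two cohorts recruited one after the other ("We will set up a single centre prospective sequential trial with two cohorts"), not randomised, so patients' fitness and the available options may change between periods. Entry also differs. In cohort 2, "We will only inform patients if they have received counselling with the model", whereas cohort 1 has no matching filter. If accepting the model goes with fitness, or with having a treatment decision to make, the shares would differ. The multivariable models named under Statistical analysis are for the total decisional conflict score and survival. The treatment outcome falls under tests chosen by variable type.

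**The case against.** The strongest reply is that the stated outcome is the amount of treatment, and receipt measures exactly that. The Background's motivating evidence is also about receipt: patients who discuss end-of-life care are less likely to get burdensome treatment. Receipt in all patients captures the total effect of the counselling strategy, including any change in what physicians propose, and it is objective. This stands, and it is why receipt should not be demoted or replaced.

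Several stronger readings are tempting but unsupported:
- A reader might infer that untreated patients are counted as having chosen less. No section says so. The issue arises only when the endpoint is read against the hypothesis.
- A reader might infer that the cohorts will be biased on this outcome. Directional bias requires the share with an option to differ; otherwise only dilution remains. Confounding between sequential cohorts also affects every outcome, and WHO performance status and ACE-27, two likely drivers, are collected at baseline.
- A reader might infer that counselling cannot affect patients who never start. Some may have delayed or reconsidered because of it.
- A reader might infer that offers and refusals are not being recorded. A condensed article does not show that; the full protocol or case report form may provide for it.

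The alternative measure has limits too. A pre-counselling offer is not guaranteed to be independent of the model, since the article expects physicians to develop a learning curve. Restricting to patients offered treatment leaves fitness differences among them.

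What the reply does not answer is the wording in Methods/design and the Conclusion. Both make a claim about choice, and receipt alone cannot support it.

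**Conclusion.** The point holds as a mismatch between a hypothesis about choice and an endpoint about receipt, for one secondary outcome. It does not show that the endpoint is invalid or that the trial fails its main purpose, and the primary outcome is untouched.

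The size cannot be determined from the article. Under the assumed rates, having 60% to 80% of patients offered treatment shrinks a 20-point change in choice to 12 to 16 points in receipt. A gap of 10 to 20 points in the share offered produces a 7- to 14-point difference in receipt with no change in choice. The dilution result requires some patients to have no option or to be unable to start. The directional result also requires that share to differ between cohorts, which the design makes plausible but does not establish. This is a cheap improvement rather than a serious defect.

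**What to change.** Keep treatment received in all patients as the secondary endpoint. In the patient-file review already planned, also record for each patient:
1. whether a tumour-directed palliative treatment was offered, taken from the tumour board advice before counselling where documented;
2. the patient's decision;
3. if treatment was not started, the reason.

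Report acceptance among patients offered treatment alongside receipt, as the analysis of the choice hypothesis. Word any conclusion drawn from receipt alone as treatment received, not treatment chosen.

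The cost is three extra fields per patient. The new measure has a smaller denominator, depends on how completely offers and refusals are noted in the files, and remains exposed to confounding between the cohorts. If the notes prove too sparse, the minimum is to reword the hypothesis and the Conclusion to treatment received.

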**Methods:**

This study will employ both quantitative and qualitative approaches. The primary outcome is decisional conflict and satisfaction with the decision-making process after counselling without (cohort 1) and with (cohort 2) OncologIQ Palliative. Therefore, a prospective sequential cohort study will be conducted. Secondary outcomes include the amount of palliative treatment, overall survival rates, and quality of life. These measurements will be collected after the intervention. Additionally, patients’ perspectives on the decision-making process and proactive care planning, including end-of-life discussions, will be explored through interviews.

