**Discussion:**

By offering more personalized prognostic information for HNSCC patients in the palliative phase, we anticipate a shift towards more patient-centred counselling. This approach can facilitate enhanced end-of-life discussions and better proactive care planning. Patients may experience reduced decisional conflict, feel better prepared for what’s coming, and find assistance in their decision-making process. This could potentially lead to fewer palliative treatments. Overall, these aspects can contribute to a better quality of life and quality of care for HNSCC patients in the last phase of their lives.

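### The secondary outcome is named the amount of palliative treatment but is derived only as treated or not and type, so fewer courses or lines within one modality cannot be seen

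*Protocol article*

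**What the plan says.** All places are in the protocol article.

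- **Name of the outcome.** Abstract, Methods: "Secondary outcomes include the amount of palliative treatment, overall survival rates, and quality of life". Methods/design gives the same name within a list of outcomes: "decisional conflict, the amount of palliative treatment, palliative sedation or euthanasia, overall survival and QoL".
- **Expected effect.** Abstract, Discussion: "This could potentially lead to fewer palliative treatments". Conclusion: the authors expect that "they will choose for less treatment in the palliative phase". The hypothesis in Methods/design is put differently: informed patients "they may choose palliative treatments less often, and it could lead to a higher QoL".
- **Derivation.** Outcome evaluation, Clinical study: palliative treatment "will be assessed by examining whether a patient underwent treatment and the type of treatment received". The source follows: "Data on treatment modalities will be collected for each patient by consulting the EPF".
- **Analysis.** Under Statistical analysis, secondary outcomes other than survival get a test that depends on whether the variable is continuous or categorical and on its distribution. No treatment count, number of lines or duration is named there or elsewhere in the article.

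**The concern.** The name of the outcome and two of the three statements of its expected effect are about quantity. The derivation is about presence and kind. A patient who starts one treatment and then declines more of the same modality is recorded exactly like a patient who takes every further course of it.

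If better prognostic information acts partly by leading treated patients to stop earlier, the derived variables can miss it. The trial could then report no difference in the amount of treatment without having measured the amount. This outcome is tied to a stated hypothesis, so how it is read matters even though it is secondary and the sample size was not set for it.

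**Working it through.** **1. The derivation applied to example records.**

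| Record | Treated | Type | Courses |
|---|---|---|---|
| A: one course of modality X | yes | X | 1 |
| B: three courses of modality X | yes | X | 3 |
| C: one course of X, then one of Y | yes | X and Y | 2 |
| D: none | no | none | 0 |

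A and B are identical under the stated derivation, although B had three times as many courses. C differs from A through type, provided all modalities are kept per patient. D differs from the rest. The blind spot is therefore a change in number within the same modality. This needs no assumed figures: if the cohorts differ only in that respect, receipt and type have the same distribution in both, and the chance of a significant result is the 5% error rate.

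**2. Illustration of size.** The article gives no figure for this outcome, so there is none to reproduce. The 80 per cohort and the 0.05 significance level come from the article. Everything else here is assumed: the share treated is the same in both cohorts, and courses per treated patient = 1 + Poisson(mean − 1). There were 4000 simulated trials per scenario. Treated-or-not is compared by chi-square and the count by Welch t-test.

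For 60% treated and means of 2.0 and 1.25, courses per patient are 0.60 × 2.0 = 1.20 and 0.60 × 1.25 = 0.75. The fall is 0.45 / 1.20 = 37.5%.

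| Treated, both cohorts | Mean courses per treated patient | Treated-or-not rejects | Count rejects |
|---|---|---|---|
| 60% | 2.0 vs 1.25 | about 5% | about 80% |
| 40% | 2.0 vs 1.5 | about 5% | about 22% |
| 80% | 2.0 vs 1.0 | about 5% | over 99% |

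**3. What the type data would recover.** Take the first scenario again, and let each later course be a new modality with probability q. Group patients as none, one modality, or several, and compare by chi-square. This grouping is not in the article; it tests only what the collected data could show.

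| q | Grouping rejects |
|---|---|
| 0.75 | about 93% |
| 0.5 | about 82% |
| 0.1 | about 20% |
| 0 | about 5% |

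**4. The same fall by the other route.** Let the share treated fall from 60% to 37.5% with 2.0 courses per treated patient in both cohorts: 0.375 × 2.0 = 0.75, again a fall of 37.5%. Treated-or-not now rejects in about 81% and the count t-test in about 65%.

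**5. Checks on a count as the outcome.**
- A raw count grows with time alive. Assume exponential survival with medians of 5 and 7 months, 60% treated, and an identical rate of 0.2 further lines per month. The count t-test then rejects in about 16% of trials although treatment intensity is the same.
- In the first scenario of step 2 a Mann-Whitney test on the count rejects in about 48%, against about 80% for the comparison of means.

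**The case against.** The strongest case against has four parts.

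- **Type is recorded as well.** A reader might infer that any reduction among treated patients is scored as no change, or that only a drop to no treatment can register. The article does not support that. It records the type received and collects modalities for each patient, so a dropped modality is visible. Step 3 shows that this can recover most of the signal when later courses are often a new modality, and little when they seldom are. This part stands and limits the concern to number within a modality.
- **Amount may mean the share of patients treated.** The hypothesis that treatments are chosen less often fits treated-or-not well, and fewer or less treatment can be read at cohort level. On that reading the derivation is sound, and treated-or-not is the more powerful comparison (step 4). This stands as a reason to keep it as a compared outcome. It does not remove the mismatch, because the name would then be wrong.
- **The article is condensed.** How modalities are tallied could be left to the full protocol or analysis plan. But the article does state a derivation, and what it states does not measure the outcome it names. That is a conflict within the text shown, not an omitted detail.
- **A null result is not certain to mislead.** A reader might infer that the trial would wrongly conclude that amount did not change. The documents do not support that either. It depends on whether the effect lies in later courses of the same modality, and the article gives no treatment rates.

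**Conclusion.** The concern holds in limited form. The named outcome is an amount; the stated derivation is receipt and type. A change in the number of courses or lines within one modality is invisible to it, and a dropped modality appears as a change of kind, not of quantity. That follows from the text alone.

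The size is illustrative. With 80 per cohort and equal shares treated, treated-or-not rejects at about the 5% error rate, while a count rejects in about 22% to over 99% of trials across the assumed scenarios. These figures rest on assumed treatment rates and a 1 + Poisson count, and the 5% applies to the treated-or-not component only. They do not show that a count is always better: if fewer patients start treatment, treated-or-not does better (about 81% against about 65%).

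The mismatch should be corrected, preferably before treatment data are abstracted, so that the definition is not chosen with results in view. It does not touch the primary outcome or the sample size.

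**What to change.** In the palliative treatment paragraph of Outcome evaluation:

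- Keep treated-or-not and type as outcomes compared between cohorts.
- Add the number of palliative treatment courses or lines started per patient, taken from the same patient files.
- Count over one fixed window from the start of the palliative trajectory, the same in both cohorts, or use time alive and followed as an offset.
- Compare the count with a log-link count model with robust or overdispersed variance.

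If no count is to be collected, rename the outcome receipt and type of palliative treatment throughout, and draw no conclusion about amount.

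The cost is a change of wording, one more field from files that are already being read, a rule for what counts as one course or line, and slightly longer abstraction. Renaming alone costs only the wording, but gives up the question about amount.
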